## Abstract

**Background:**

The concept of deprescribing is gaining traction among clinicians as a formalized approach to improving medication safety for older persons. It has been found to be safe and effective in reducing medication burden. However, its implementation remains challenging. Most research has been conducted in high-income countries, with limited prospective data on deprescribing outcomes in outpatient care settings for older adults in low- and middle-income countries (LMICs). Therefore, evaluating local deprescribing interventions is essential to produce evidence on their effectiveness in older populations. Our study aimed to assess the effectiveness of the Physician-Pharmacist Partnership Intervention for Deprescribing (P3ID) among older persons attending a falls and syncope clinic.

**Methods:**

This randomised controlled trial will be conducted at a teaching hospital in Kuala Lumpur, Malaysia. Participants will involve individuals aged ≥60 years with at least one chronic disease requiring pharmacological treatment, attending the falls and syncope clinic with ≥1 potentially inappropriate medication (PIM) undergoing systematic multidomain assessment and attending physicians at the clinic. The joint pharmacist-physician intervention comprises five steps: 1) PIM identification, 2) decision on cessation and prioritisation, 3) medication withdrawal, 4) monitoring and support, 5) and documentation.

**Conclusion:**

The P3ID trial tests the hypothesis that a jointly led pharmacist-physician intervention in an outpatient will reduce the total number of medications, improve medication adherence, reduce falls and improve patients’ and doctors’ satisfaction towards pharmacist services. Findings from this study would inform future deprescribing practices, particularly in LMIC, pertaining to fall prevention as well as aid the development of future deprescribing interventions in other settings.

## Introduction

Deprescribing is defined as “the process of withdrawal of an inappropriate medication, supervised by a healthcare professional with a goal of managing polypharmacy and improving outcomes” [1]. One in five medications prescribed to older persons are considered inappropriate [2]. In Malaysia, 13.6% of older persons attending an outpatient clinic have been prescribed at least one potentially inappropriate medication (PIM) [3]. PIMs are associated with an increased risk of adverse drug events, increased healthcare utilisation, prolonged hospitalization and increased mortality, especially in older persons with multiple chronic conditions [4].

The recognition of harms caused by PIMs has led to research and clinical practice interventions targeted at deprescribing PIMs [1] Several deprescribing tools and interventions, such as medication reviews by pharmacists, PIM identification tools, and patient education materials are available to aid deprescribing in clinical practice [5–7]. A previous systematic review found that pharmacist-led deprescribing interventions were effective in reducing PIM use and medication burden for older ambulatory adults [8]. Pharmacists are valuable collaborators in deprescribing and are capable of leading deprescribing interventions by providing necessary monitoring throughout the tapering and monitoring processes [9].

The concept of deprescribing concept is also now increasingly popular among clinicians as a formalised approach to improving medication safety for older persons. Based on a feasibility study conducted using a physician-pharmacist partnership intervention developed in a primary care setting, deprescribing was successfully performed in 53% of PIMs found in older persons attending the clinic [10]. A systematic review found that deprescribing was safe and reduced number of medications as well as improved health-related quality of life (HRQOL), reduced healthcare costs, and hospitalization [11]. However, despite these promising outcomes, the review also highlights a critical gap: most of the evidence comes from high-income countries, with limited data available from low- and middle-income countries (LMICs). Furthermore, the lack of prospective outcome data on deprescribing in outpatient settings—where the majority of older persons are managed—remains a significant barrier to widespread implementation, particularly in resource-limited settings. This underscores the importance of evaluating deprescribing interventions in LMICs. By generating local evidence on its effectiveness in improving clinical outcomes and reducing medication burden in older adults, particularly in the falls and syncope clinic, this study will provide critical insights into how deprescribing can be optimized and scaled in LMIC contexts. Hence, our study aims to determine the effect of a Pharmacist-Physician Partnership Intervention for Deprescribing (P3ID) on reducing the total number of prescribed medications among older adults attending a falls and syncope clinic. In addition, the secondary outcomes of medication adherence, fall occurrence, rate of falls and patients’ and doctors’ satisfaction will also be evaluated.

## Materials and methods

### Study design and setting

A randomised controlled trial will be conducted at a teaching hospital. This hospital serves as a general hospital for around 300,000 people in its immediate catchment and provides tertiary services to public and private hospitals nationwide. The falls and syncope clinic receives referrals from various sources, including the emergency department, general practitioners, primary care doctors, specialist outpatient clinics, and hospital wards, both from within the hospital and from other community and hospital settings [12]. All patients referred to the clinic will be classified as high risk for falls and will undergo a multidomain risk assessment, including a medication review, in accordance with the World Guidelines for Falls Prevention and Management in Older Adults [13].

### Participants

There will be two main groups of participants in this study: patients and physicians.

#### Patients.

Individuals aged ≥60 years with at least one chronic disease requiring pharmacological treatment attending the falls and syncope clinic with ≥1 PIM according to the STOPPFall criteria [14] undergoing systematic multidomain assessment will be included. Researchers and their attending physician assessed participants’ capacity to provide informed consent for this study based on clinical judgment and provided training on mental capacity assessments. Written informed consent is obtained from participants who are deemed to have capacity. For those who lack mental capacity, assent is obtained from their next of kin. For those who may lack mental capacity, assent will be obtained from their next of kin. Since medication review and deprescribing are generally considered appropriate for older adults, no exclusion criteria are anticipated. However, consent will be sought from the physician overseeing the participant’s care, who will also be recruited into the study. If the physician determines that participation in the RCT is unsuitable for the participant based on clinical judgment, the participant will be excluded. We acknowledge the challenges of including older adults with cognitive impairment in falls prevention studies, but believe it is important for real-world relevance; while past interventions like Shaw et al. 2003 [15] focused on multifactorial strategies, deprescribing studies have shown feasibility and safety in this population with proper safeguards [16–18]. Although inclusion may attenuate the intervention effect, our approach prioritises external validity, with caregiver support and adapted data collection methods ensuring reliable participation and outcomes [19,20]. Additionally, if a potential participant’s physician declines to participate and the participant chooses to remain under their care, the participant will also be excluded.

#### Physicians.

Geriatricians, internal and family physicians undergoing subspecialty training in geriatric medicine and medical officers working at the centre will be recruited.

### Sample size calculation

Sample size was calculated using the Open Source Epidemiologic Statistics for Public Health (OpenEpi version 3.01) [21]. A search of published literature found that the mean change in the number of prescribed medications at 12 months was −1.9 ± 4.1 in intervention group participants and +0.1 ± 3.5 in control group participants [22]. Hence, the minimum number of participants needed with a two-sided confidence level of 95%, and 80% power will be at least 58 participants in each group [21]. Assuming a 20% attrition rate [23], the total number of 70 participants will be recruited to each arm.

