**Fig 1 pone.0324565.g001:**
[figure not shown]
Flowchart on the five-steps of the physical-pharmacy partnership in deprescribing intervention.

The researcher will review potential participant’s electronic medical records (EMR), if available, on the day before their appointment. The researcher will first approach the physician attending to the potential participant to determine suitability for the study before approaching selected potential patients to explain the purpose of the study. If the individual agrees to participate in the study, they will be randomised to an intervention (deprescribing) or control group (usual care) in a 1:1 ratio using a computerized random number generator in Microsoft Office® Excel® (Washington, United States of America) [24]. Participants randomized to the control group will continue to receive usual care, where medications will be reviewed and prescribed by their physician. Meanwhile, patients in the intervention group will receive an in-depth medication review performed by a pharmacist, which will focus on identifying PIMs as opportunities for deprescribing. In the intervention arm, a registered pharmacist will perform medication reconciliation using a structured medication list. However, in the control group, physicians will rely on electronic medical records and routine medication history-taking. PIMs identified in the intervention group will be deprescribed using the P3ID intervention, as shown in Participants will be followed up over 6 months (Fig 2). To assess the primary outcome, the number of prescribed medications will be determined by reviewing the patient’s medications through EMR and patient interviews via telephone calls at 3 months and 6 months. Medication adherence will be assessed using PMAI-9 and HMAI-9 via telephone calls at 3 months and 6 months. All participants will be requested to record any adverse drug reactions (ADR) due to their prescribed medications. For those undergoing deprescribing, they will be informed about the potential of withdrawal-related adverse effects, such as the return of previous symptoms or other withdrawal reactions. They will be asked to monitor and record any such symptoms. and asked to record these symptoms or withdrawal reactions. They will also be advised to see a doctor if they feel unwell or notice any unexpected adverse effects after stopping the medication.

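### The 80% power is calculated from a published 12-month difference, but the primary outcome is measured only at 3 and 6 months, so that power is not shown to apply

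*Protocol article*

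**What the plan says.** Under Sample size calculation, the protocol article bases its number on a published "mean change in the number of prescribed medications at 12 months". The values are "1.9 ± 4.1 in intervention group participants and +0.1 ± 3.5 in control group participants" (a minus sign precedes the first figure), so the planning difference is 2.0 medications. With a "two-sided confidence level of 95%, and 80% power", the article arrives at 58 per arm. It then allows for 20% attrition and recruits 70 per arm.

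Under Procedure, "Participants will be followed up over 6 months". The number of prescribed medications, which is the primary outcome, is obtained from the electronic record and from "patient interviews via telephone calls at 3 months and 6 months". Table 1 lists no instrument later than 6 months.

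Under Data analysis, the primary outcome is treated as continuous and compared by repeated measures analysis of variance. Unadjusted analyses come first, and confounders are to be chosen later from published evidence and clinical judgement.

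**The concern.** A power statement belongs to a particular effect, SD and time point. Here both the effect and the SDs describe change over 12 months, and the trial has no 12-month measurement. The article quotes the horizon of its source but does not say why a 12-month difference should be expected by 6 months, or why the spread of individual changes should be the same at half the interval.

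The design has little room for error. The 58 per arm is the minimum for a difference of 2.0, so power drops below 80% if the 6-month difference is smaller and the SD does not shrink with it. What is at stake is how a non-significant result would be read: someone relying on the stated 80% could take it as an adequately powered negative finding when the planning basis does not establish that.

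**Working it through.** **Inputs.** Sample size calculation: difference Δ = 0.1 − (−1.9) = 2.0; SDs 4.1 and 3.5; two-sided 5%; power 80%; attrition 20%; 70 recruited per arm. Procedure: 1:1 allocation; primary outcome at 3 and 6 months.

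**Step 1: reproduce the plan's figure.**

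- Sum of variances: 4.1² + 3.5² = 16.81 + 12.25 = 29.06. Root-mean-square SD = √(29.06/2) = 3.81.
- n per arm = 29.06 × (1.960 + 0.842)² / 2.0² = 57.02, rounded up to 58. The t-test version also gives 58.
- Power at 58 per arm: 80.0% (t-test), 80.7% (normal approximation).

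The stated 58 is right for its inputs.

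**Step 2: the number expected at the end.** 70 × (1 − 0.20) = 56 per arm. The recruited 70 matches 58 × 1.2 = 69.6; dividing instead gives 58/0.80 = 72.5, or 73. The calculations below use 56.

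**Step 3: power at 56 per arm for a range of 6-month differences, SDs unchanged.** The standard error is 3.81 × √(2/56) = 0.720. The noncentrality is λ = Δ/0.720 and the critical t on 110 degrees of freedom is 1.982.

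| Difference at 6 months | λ | Power |
|---|---|---|
| 2.25 | 3.12 | 87% |
| 2.0 | 2.78 | 78.6% |
| 1.75 | 2.43 | 67% |
| 1.5 | 2.08 | 54% |
| 1.0 | 1.39 | 28% |

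The article gives no 6-month difference, so this range is an assumption. The first row is included because a larger 6-month effect is not excluded.

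**Step 4: how far a smaller SD would compensate.** At 56 per arm and SD 3.81, 80% power corresponds to a difference of 2.04. Power depends on Δ/SD, so the SD that keeps 80% is 3.81 × Δ/2.04. That is about 3.3 for a difference of 1.75, 2.8 for 1.5 and 1.9 for 1.0. The article gives no SD of change at 6 months.

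**Step 5: what baseline adjustment would add.** Let σ² be the variance of the count, equal at baseline and 6 months, and ρ their correlation. The change score has variance 2σ²(1 − ρ). The baseline-adjusted count has variance σ²(1 − ρ²). The ratio is (1 + ρ)/2. With the change-score SD held at 3.81 and 56 per arm:

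- ρ = 0.7: ratio 0.85, standard error 0.720 × √0.85 = 0.664, λ for 2.0 = 3.01, power about 85%.
- ρ = 0.8: ratio 0.90, standard error 0.720 × √0.90 = 0.683, λ for 2.0 = 2.93, power about 83%.

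The values of ρ are assumptions; the article gives none. The gain is useful but does not settle the question of horizon: for a difference of 1.5 with ρ = 0.7, λ = 1.5/0.664 = 2.26 and power is about 61%.

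**The case against.** The best defence is that the direction of any error is unknown. The Discussion notes that withdrawn drugs may be restarted when disease or symptom control suffers, so a 6-month reduction could match or exceed the 12-month one. Change over a shorter interval may also vary less, which would help power. A condensed article may leave the bridging argument to the full protocol. The first two points stand, and they limit the conclusion to *not shown to apply*. The third carries less weight: the article itself states the power and the horizon behind it, and as written the two do not match the trial's own measurements.

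A reader might infer stronger criticisms that the documents do not support.

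- *That the planned effect contradicts the feasibility result, in which "deprescribing was successfully performed in 53% of PIMs found in older persons attending the clinic".* That figure is a proportion of potentially inappropriate medications (PIMs); the planning value is a mean change in all prescribed medications. They agree if patients carry about 2.0/0.53 = 3.8 PIMs each. The article gives an entry minimum of one and no mean, so there is no demonstrated conflict, and power figures built on guessed PIM counts would only reflect the guesses.
- *That the planning value has the wrong control condition, because all clinic patients "will undergo a multidomain risk assessment, including a medication review", or that it comes from another setting.* The article describes neither the setting nor the control care of the cited study, so neither mismatch can be established.
- *That the trial is underpowered.* This would need a 6-month effect and SD, and the article gives neither.

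**Conclusion.** The point holds in a limited form. The 80% power is correctly computed for a 12-month difference of 2.0 with SDs 4.1 and 3.5. The trial measures at 3 and 6 months, and the article gives no reason to carry those values over, so the power is not shown to apply to the primary outcome.

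The size depends on unknowns. If the 12-month values do hold at 6 months, the shortfall is small: 78.6% at the expected 56 per arm. If the 6-month difference is 1.5 with the same SDs, power is 54%; if it is 1.0, 28%. A smaller SD or a larger early effect would move these figures up. The defect lies in the stated justification; the documents do not show that the sample is too small.

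**What to change.** Two changes, neither needing more patients.

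1. **Sample size calculation.** State that 2.0 and its SDs are 12-month planning values, and either justify their use at 6 months or say that they are assumed. Give power at the 56 per arm expected after 20% loss from 70: 78.6% for 2.0, 67% for 1.75, 54% for 1.5 and 28% for 1.0 with the SDs unchanged, noting that a smaller 6-month SD would raise these.

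2. **Data analysis.** In place of the repeated measures analysis of variance, make the primary between-group comparison the 6-month medication count adjusted for the baseline count, by ANCOVA or an equivalent mixed model. The medication history is already recorded at baseline on the patient assessment form (Table 1), so no new data are needed. State the assumed correlation behind any power claimed for this analysis.

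The cost is one paragraph and one amended sentence, to be fixed before outcome data are examined. The stated unadjusted power becomes less favourable; the adjusted analysis recovers some of it.

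### With the stated 20% attrition, 70 per arm leaves 56 evaluable, two below the stated minimum of 58: a minor arithmetic error worth about one point of power

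*Protocol article*

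**What the plan says.** The Sample size calculation section of the protocol article gives the whole chain in one paragraph. The planning values are taken from a published study of the change in the number of prescribed medications at 12 months: a decrease of "1.9 ± 4.1 in intervention group participants" and an increase of "0.1 ± 3.5 in control group participants". The error rates are a "two-sided confidence level of 95%, and 80% power". The result is "at least 58 participants in each group". The allowance for loss follows: "Assuming a 20% attrition rate", and then "the total number of 70 participants will be recruited to each arm". The Procedure section confirms equal allocation, with participants randomised to the intervention or "control group (usual care) in a 1:1 ratio". The article gives no other recruitment target, no other attrition rate, and no reason for accepting fewer than 58 evaluable participants per group.

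**The concern.** The paragraph sets a floor of 58 per group and then a recruitment target that falls below that floor once its own attrition assumption is applied. A 20% mark-up on the required number is not the same as an allowance for losing 20% of those recruited: the loss applies to the larger, recruited number, so the required number must be divided by the retained fraction. At stake is the accuracy of a headline design figure. If the final report repeats 70 per arm, 20% attrition and 80% power together, it repeats a combination that does not hold and that any reader can check.

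**Working it through.** **Inputs**, all from the Sample size calculation section except the allocation ratio (Procedure section):

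- Difference in mean change: 0.1 − (−1.9) = 2.0 medications
- Standard deviations: 4.1 (intervention) and 3.5 (control)
- Two-sided alpha 0.05 (z = 1.96); power 80% (z = 0.8416)
- Allocation 1:1
- Attrition 20%

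**Step 1. Reproduce the stated minimum.**

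n per group = (1.96 + 0.8416)² × (4.1² + 3.5²) / 2.0² = 7.849 × 29.06 / 4 = 57.02, rounded up to 58.

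This matches the article exactly.

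**Step 2. Apply the attrition allowance to 58.**

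- Dividing by the retained fraction: 58 / (1 − 0.20) = 72.5, rounded up to 73 per arm (146 in total).
- Multiplying by one plus the rate: 58 × 1.20 = 69.6, rounded up to 70 per arm (140 in total).

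Only the second gives the stated 70. Reaching 70 by division would need a base of 56 (56 / 0.8 = 70), and the article states no such base.

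**Step 3. Check the stated target against the stated minimum.**

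- Evaluable at 20% attrition: 70 × 0.80 = 56 per arm, against 58 required; shortfall 58 − 56 = 2 per arm.
- Largest attrition that still leaves 58: 1 − 58/70 = 12/70 = 17.1%.

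**Step 4. Power for a two-group comparison of completers**, with difference 2.0 and pooled SD √(29.06 / 2) = 3.81.

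Normal approximation: power = Φ(2.0 / √(29.06 / n) − 1.96). At n = 56 this is Φ(2.776 − 1.96) = Φ(0.816) = 79.3%. The t-test column uses the noncentral t distribution with 2n − 2 degrees of freedom.

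| Evaluable per arm | Normal approximation | t-test |
|---|---|---|
| 56 | 79.3% | 78.6% |
| 57 | 79.98% | 79.3% |
| 58 | 80.7% | 80.0% |
| 70 (no loss) | 87.4% | 86.9% |

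The stated 58 carries no slack: 57 is already just below 80% on either calculation. The shortfall at 56 is 80 − 79.3 = 0.7 points (normal approximation) or 80 − 78.6 = 1.4 points (t-test).

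**Step 5. Sensitivity to rounding order.** Inflating the unrounded requirement gives 57.02 / 0.8 = 71.3, or 72 per arm. The recruitment deficit is therefore 2 or 3 per arm, depending on whether rounding comes before or after inflation. Starting from the article's own 58, it is 3.

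**The case against.** The strongest reply is that this hardly matters, and as to size that is right. A loss of 0.7 to 1.4 points of power is small beside the uncertainty in the planning values, which come from a 12-month result while this trial follows participants for 6 months. A reader might infer from the error that the trial is materially underpowered; the figures do not support that. If fewer are lost than assumed, power is higher, up to about 87% with no loss.

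A second reply is that the completer comparison is not the planned analysis. The Data analysis section names repeated measures analysis of variance for the primary outcome, an intention-to-treat basis, and multiple imputation in some missing-data situations. The Procedure section takes the medication count from electronic records as well as telephone interviews, so someone lost to telephone contact may still have outcome data. These points stand as qualifications: 79% is the power of the comparison used to derive 58, not a prediction for the final analysis. They do not remove the inconsistency, because the article itself treats attrition as a loss to be compensated by recruitment and nowhere claims that the analysis regains it. Likewise, a reader might infer that adjustment for the baseline count would make up the shortfall. The article gives no correlation between baseline and follow-up counts, so no figure can be put on that.

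Third, the article does not show the inflation step. That 58 was multiplied by 1.2 is an inference, though a very plausible one, since 69.6 rounds to 70. The point does not depend on it: 70 × 0.8 = 56 however 70 was reached.

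**Conclusion.** The point holds as a minor arithmetic error in a stated design figure. Under the article's own 20% attrition, 70 per arm leaves 56 evaluable, two below its own minimum, with power of about 79% instead of 80%. This takes as given the stated difference of 2.0 and SDs of 4.1 and 3.5, attrition of the full 20% in both arms, and an unadjusted comparison of completers. A flat statement that the trial misses 80% power would go too far, because it depends on attrition above about 17% and on that form of analysis. What is wrong as written is that the target, the attrition rate and the power are presented as consistent, and they are not.

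**What to change.** Correct the last sentence of the Sample size calculation section in one of two ways, neither of which changes recruitment:

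- state that 70 per arm allows for about 17% attrition while keeping 58 evaluable; or
- keep 20% attrition and state that 70 per arm leaves 56 evaluable, with about 79% power for a difference of 2.0 medications.

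For reference, if the sponsor wishes to keep both 20% attrition and the stated minimum of 58, the target is 73 per arm (146 in total), since 73 × 0.8 = 58.4. That means 3 more recruits per arm, 6 in all. Either rewording costs one sentence and a slightly less favourable statement of power or attrition. The final report should carry the corrected wording.
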